Our research group has previously done an *in vitro* study in which we analyzed the effect of FLZ and the antiseptic substance chlorhexidine gluconate’s (CHG) ability to kill fungal cells and to break down existing biofilm or prevent new biofilm formation [9]. The biofilm formation is an important stage for the fungal cells to attach to surfaces such as skin and mucosa and is considered a first step in the development of an infection [10]. In the biofilm, the fungus can hide from the immune system and also to some extent for various treatments aimed against the fungus. The results of the study showed that CHG was better than FLZ both at killing the fungal cells and preventing new biofilm from forming and dissolving already established "old" biofilm. This effect is absolutely crucial for successful treatment with antimycotics. These encouraging results form the basis of the planned study.

Hibitane® is an over-the-counter vaginal cream consisting of 1% chlorhexidine gluconate with the indication antiseptic use in vaginal examinations, especially during childbirth. The product has been used for a long time in various gynecological and obstetric surgical procedures. Hibitane® is approved during pregnancy and the cream is usually well tolerated [11]. There are only few studies that investigated how vaginal normal flora is affected by CHG. One human study showed a decrease in the number of lactobacilli a week after the vaginal application of 0.5% CHG every night for a week. After 30 days, the vaginal normal flora was basically fully recovered and the side effects were few [12]. In an animal study, no major effect was seen on the vaginal flora after 2 vaginal applications of CGH 0.25% at 24 hours apart [13].

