## Secondary endpoint (variables)

1. The proportion of women in each group that has negative vaginal cultures for *Candida albicans* at 3 months’ follow-up after prophylactic treatment and at 6 months’ follow-up after the observational phase of the study.
2. Analysis of proportion of women with adverse events (AE) across treatment arms. The AEs will also be reported in descriptive terms and summarized for each treatment arm.
3. Proportion of women with symptom score > 2. Each symptom of typical discharge, itching, dryness of the skin/mucosa, burning and pain will generate 1 point of a composite index (range 0-5).
4. Proportion of women with examination score >2. Each finding of redness skin/mucosa, typical discharge, dry skin/mucosa, fissures skin/mucosa, visible candida hyphae in the microscope will generate 1 point of a composite index (range 0-5).
5. Proportion of women with reduced vaginal lactobacilli content in vaginal smears measured by a semi-quantitative method as normal or reduced quantity.
6. Proportion of women with relapse of *Candida albicans* infection between end of treatment and end of prophylactic treatment (1week post treatment to 3 months’ follow-up) and between 3- and 6 months’ follow-up after end of prophylactic treatment.
7. Proportion of women with possible toxic effect on the vaginal epithelium, defined as disruption and/or inflammation of the epithelial lining, analyzed from vaginal biopsies before and after treatment and prophylaxis.
8. Further analysis of mucosa inflammatory mechanism (histopathology and immunohistochemistry) and biofilm formation during and after treatment and prophylaxis, analyzed from vaginal biopsies. The methods for these *in vitro* exploratory analyses are not yet decided on.

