## Procedures and flow chart

**Five research visits are planned:**

**Visit 1** Screening – oral and written study information, signing of informed consent, vaginal culture for Candida albicans and chlamydia/gonorrhea (PCR test). 45 min.

**Visit 2** Inclusion (baseline), within 1 week after Visit 1. Control for inclusion/exclusion criteria, randomization to study medication after positive culture for *Candida albicans* and negative chlamydia/gonorrhea (PCR test) – health survey, control of concomitant medications, examination, vaginal biopsies, pregnancy test and control of adequate contraceptive methods to avoid pregnancy throughout the study. 1 h.

**Visit 3** 1 week (+2 days) after completed treatment. Control of AE, culture for *Candida albicans* and examination (no biopsies). 30 min.

**Visit 4** After 12 weeks (+ 1 week) from inclusion when prophylactic treatment is completed. Control of AE and relapses, culture for *Candida albicans* and examination, vaginal biopsies. 45 min.

**Visit 5** Follow-up 6 months (+ 1-2 weeks) from baseline/inclusion. Control of AE and relapses, culture for *Candida albicans* and examination (no biopsies). End of study. 30 min.

A weekly web-based dairy (eCRF (Entermedic)) will be used for follow-up of treatment

compliance, efficacy and adverse events. A personal link will be sent via e-mail every week

from week 2-24. During the prophylactic treatment (Visits 2-3) and during the observational

phase of the study (Visit 4-5), the participants are asked to report any suspicious relapses in

the dairy and contact the research midwife if needed. They will also receive equipment for

vaginal cultures that can be used for self-sampling at home to detect true relapses. In case of

positive cultures for *Candida albicans*, they will be offered the same medication as previously

used in the study if the treatment was effective and no adverse events occurred. Otherwise,

an individual treatment option will be used.

Table 1 Flow chart

| **Procedure** | **Visit 1**  Screening  Week -1 | **Visit 2**  Baseline/  inclusion  Week 0  (within 1 w from Visit 1) | **Visit 3**  Follow-up  Week 1  (treatment)  (+2 d) | **Visit 4**  Follow-up  Week 12  (prophylactic phase)  (+1 w) | **Visit 5**  Follow-up  Week 24  (observational phase)  (+2 w) |
| --- | --- | --- | --- | --- | --- |
| Incl/exclusion criteria | √ | √* |  |  |  |
| Informed signed consent | √ |  |  |  |  |

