## Dose and administration

1. Hibitane® is a cream and will be applied vaginally by the help of a 10 ml plastic syringe (Braun, Melsungen, Germany, CE 0123), provided to the participants randomized to Hibitane®. During the first week of treatment 8 ml is used every night at bedtime and thereafter 8 ml will be used at night once a week for 11 consecutive weeks. The dose of 8 ml is considered an adequate to be applied in the vagina for achieving treatment effect. Most of the cream will stay in place, but a small portion will leak and a genital pad is recommended. Dose changes or withdrawal of the medication will be considered in case of AE.
2. Fluconzole® oral 150 mg capsules will be used every 3 days for the first 3 doses, thereafter as prophylactic treatment with 150 mg/week for another 11 consecutive weeks. The fluconazole regime serves as the reference medication normally used for recurrent vulvovaginal candidiasis according to international recommendations and FASS. Fluconazole can be taken regardless of food intake. Dose changes or withdrawal of the medication will be considered in case of AE.

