4. The content of lactobacillus in vaginal wet mount will be analyzed and semi-quantified first at baseline/inclusion and then at 3 follow-ups; 1 week after treatment, 3 months’ follow-up after prophylactic treatment and at 6 months’ follow-up. Routine procedure for wet mount (vaginal secretion with NaCl) will be performed and the amount of lactobacilli will be graded in a light microscope with high magnification (40x and 100x) (Olympus CX41) as either normal quantity (more lactobacilli compared to number of epithelial cell/view field) or reduced (less or absent lactobacilli compared to number of epithelial cell/view field). Differences in proportion of women with normal/reduced quantity between study groups x time will be analyzed. The two investigators will before the study starts, analyzed a number of wet mounts together for inter-rater reliability. All wet mounts will be photo documented via a camera connected to the microscope placed at the department of obstetrics and gynecology, Danderyd Hospital. These photos will be blinded and evaluated by the two investigators together.
5. Data on events of relapses will be collected during the prophylactic and observational phases of the study. The participants will be provided with equipment to collect self-sampled vaginal cultures for *Candida albicans* at home in case of new symptoms of infection. They can also contact the research midwife who could help out with the cultures if needed. Data on relapses will be reported in the CRF.
6. Biopsies from the vaginal mucosa will be used to study possible toxic effect on the vaginal epithelial cells. The biopsies will be taken at baseline/inclusion and at the 3 months’ follow-up and analyzed by histopathology and immunohistochemistry. The biopsies are 3-4 mm, taken by biopsy forceps after local anesthetics. The purpose of the biopsies is to investigate how CHG affect the vaginal mucosa causing possible toxic reactions of the epithelium and impairment of the local immune response. The biopsies will be microscopically examined using ordinary histopathological staining as well as immunohistochemistry for inflammatory and immunological markers. Also PCR analyses for antimicrobial peptides, cytokines, kemokins, cationic intrinsically disordered antimicrobial peptides (CIDAMP) will be performed. Biopsies from participants allocated to FLZ will serve as controls.

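### Relapse swabs during prophylaxis are not timed against the weekly chlorhexidine cream, so false-negative cultures could tilt the 1-week-to-3-month relapse comparison towards CHG

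*Protocol*

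**What the plan says.** **Endpoint.** Secondary endpoint 6 is the proportion of women with relapse of *C. albicans* "infection between end of treatment and end of prophylactic treatment (1week post treatment to 3 months’ follow-up) and between 3- and 6 months’ follow-up". It therefore has two windows, the prophylactic phase and the observational phase.

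**How relapse is established.** Section 8.1.2, item 5 says "The participants will be provided with equipment to collect self-sampled vaginal cultures for" *C. albicans* "at home in case of new symptoms of infection". Procedures and flow chart gives the purpose: equipment for "vaginal cultures that can be used for self-sampling at home to detect true relapses". There are other routes to a culture. Item 5 adds: "They can also contact the research midwife who could help out with the cultures if needed". Visits 4 and 5 each list "Control of AE and relapses, culture for" *C. albicans*.

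**What is in the vagina at the time.** Under Dose and administration, CHG women insert 8 ml of cream nightly for a week and then once a week for 11 weeks. The protocol says: "Most of the cream will stay in place, but a small portion will leak and a genital pad is recommended". Background and rationale reports from the group's in vitro study that "CHG was better than FLZ both at killing the fungal cells". FLZ women take a weekly oral capsule over the same weeks. Vaginal clotrimazole appears in either arm only as rescue.

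**What is recorded.** A weekly web diary covers how study medication was taken, and suspected relapses are reported in it (Drug accountability and treatment compliance; Procedures and flow chart). No section sets an interval between application and swab, asks for the date of the last dose with a swab, or mentions residual antiseptic in the specimen.

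**The concern.** The trial is open, and the protocol defends its primary outcome against bias on the ground that a culture is objective. For relapse, that defence needs the culture to detect infection equally well in both arms. In the prophylactic phase one arm places an agent that kills *Candida* at the site from which the specimen is taken, and the other arm swallows a capsule. If cream carried on the swab suppresses growth in the laboratory, an infected woman on CHG reads as negative and is not counted as a relapse.

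Such an error would lower the observed relapse rate in the experimental arm only, in a trial that asks whether CHG is at least as effective, including as prophylaxis. If the interval between dose and swab is not captured when the swab is taken, the bias can be neither measured nor reliably excluded afterwards.

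**Working it through.** The protocol gives no relapse rate, carry-over time or false-negative rate, so it has no figure on this point to reproduce. Its sample size (section 10.4) concerns the 1-week culture and is not used here.

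**1. Which cultures can follow a CHG application closely?**

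| Culture | Scheduled cream beforehand | Timing rule against last dose |
|---|---|---|
| Home or midwife swab, 1 week to 3 months | weekly | none |
| Visit 4, week 12 (+1 week) | last weekly dose due at about this time | none |
| Home or midwife swab, 3 to 6 months | none, unless re-treated with CHG | none |
| Visit 5, month 6 | none, unless re-treated with CHG | none |

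For Visit 4, assume that the first weekly dose comes 7 days after the last nightly dose on night 7. The eleventh weekly dose then falls on night 7 + 11 × 7 = 84. Visit 4 is due from day 12 × 7 = 84 to day 91, so the culture may be taken 0 to 7 days after the last cream. If weekly dosing starts sooner, the gap widens by the same number of days.

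**2. How large could the effect be?** The following inputs are assumptions, not taken from the documents:
- w: days after a dose in which residue can affect the culture (1 to 3)
- f: chance of a false negative in those days (0.25 to 1.0)
- swab days spread evenly over the dosing week
- one swab per relapse, never repeated
- a true relapse risk of 30% in both arms

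Missed share m = (w/7) × f. Observed CHG relapse = 0.30 × (1 − m). Each cell gives m, then observed CHG relapse.

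| w (days) | f = 0.25 | f = 0.5 | f = 1.0 |
|---|---|---|---|
| 0 | 0; 30% | 0; 30% | 0; 30% |
| 1 | 3.6%; 28.9% | 7.1%; 27.9% | 14.3%; 25.7% |
| 2 | 7.1%; 27.9% | 14.3%; 25.7% | 28.6%; 21.4% |
| 3 | 10.7%; 26.8% | 21.4%; 23.6% | 42.9%; 17.1% |

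Excluding w = 0, the range is 4% to 43% missed. With 30 women and 30 × 0.30 = 9 true relapses, the missed number is 9 × m: 0.3 women at the low end, 1.3 at w = 2 and f = 0.5, and 3.9 at the high end.

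**3. What would a repeat swab do?** If a missed relapse is swabbed again at an independent time in the dosing week, the share still missed is m². The middle case falls from 14.3% to 0.143² = 2.0%, and the upper case from 42.9% to 0.429² = 18.4%. A positive Visit 4 culture could lower it further.

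**4. Scale.** The standard error of the difference at 30 per arm and 30% relapse is √(2 × 0.30 × 0.70 / 30) = 0.118, or 11.8 points. The middle case shifts the difference by 30 − 25.7 = 4.3 points, and the upper case by 30 − 17.1 = 12.9 points.

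**The case against.** The strongest reply is that the protocol contains no evidence of carry-over. The remark about cream staying in place concerns leakage after a bedtime application, not residue days later. The in vitro result concerns killing of fungal cells, not suppression of growth from a swab. If carry-over is nil, so is the bias. The even spread of swab days is also assumed: if the cream suppresses *Candida* briefly, symptoms might return late in the dosing week, away from the dose. This stands, and it is why no size can be claimed.

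A reader might infer several stronger things that the documents do not support:

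- *That a relapse requires a positive home swab.* The midwife can help with cultures, and Visits 4 and 5 include one. These cultures have no timing rule either, so they soften the problem without removing it.
- *That both relapse windows are affected.* No cream is scheduled from 3 to 6 months.
- *That dosing goes unrecorded.* The diary covers how medication was taken. What is missing is a stated link between swab date and dose date.
- *That a false negative bars a woman from care.* Re-treatment and rescue are tied to a positive culture, but the protocol also allows medication that the investigator considers necessary.
- *That FLZ cultures are shown to be unaffected.* These women are also on an antifungal. Suppression of infection by a systemic drug is, however, treatment effect; antiseptic carried into the specimen is measurement error.

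Swab instructions may also sit in participant material that is not shown. The protocol nevertheless specifies the wet mount in the same section down to magnification, so a timing rule for the swab would belong there.

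**Conclusion.** The concern holds in a limited form. The plan as written allows a one-sided false-negative error in the relapse comparison from 1 week post-treatment to 3 months, and in the Visit 4 culture. If the error occurs, it favours CHG. It rests on three documented facts: relapse is confirmed by culture, only the CHG arm has a vaginal antiseptic scheduled in those weeks, and no rule or record ties swab to dose.

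The size is unknown and may be nil. The 4–43% range illustrates assumed carry-over with a single unrepeated swab per relapse; it is not an estimate. The middle case, about 1 woman in 30, is well below the sampling error of the comparison.

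The outcomes affected are secondary, and section 10.3 places them under false discovery rate control. That control limits chance findings and does nothing about a directional measurement error. The primary culture at 1 week is outside this point. A correction is worth making because it is cheap and because a missing interval cannot be reliably recovered later.

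**What to change.** Leave dosing unchanged and make three additions.

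1. In the self-sampling instruction, for both arms: take a relapse swab before, not after, any study dose due that day.
2. On the swab form, for both arms: record the date of the swab and the date of the last study dose. Do this for every relapse swab, whether taken at home or with the midwife, and for the Visit 4 culture.
3. Report prophylactic-phase relapse and the 3-month culture result with a sensitivity analysis in which negative cultures taken within a pre-specified number of days after a vaginal application count as not evaluable. Fix that number before the data are seen.

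The sensitivity analysis will set aside negatives mainly in the CHG arm, so it pushes against CHG. Read it beside the main analysis, as a bound and not a replacement.

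Any rule for repeating swabs must apply equally to both arms. Repeating only negative CHG swabs would give that arm extra chances to turn positive and replace one bias with the opposite one.

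The cost is one more instruction, one form field and one sensitivity analysis.

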## Overall study design

The study is a 6 months clinical Phase II trial to compare if 1% chlorhexidine gluconate vaginal cream (Hibitane®) is at least as effective and safe as fluconazole (reference treatment) for culture-verified recurrent vulvovaginal candidiasis. The study is a randomized open non-inferiority trial with parallel treatment groups. The trial is not possible to blind for neither participants nor investigators due to the differences between study treatments. There is low risk of bias since the primary outcome variable is objective (negative vaginal culture for *Candida albicans*).

The rational for the study is to find an alternative treatment to fluconazole for RVVC with high tolerability and without cytotoxic effect on epithelial cells and negative impact on the vaginal microbes.

The participants will be randomization to;

- Investigational medication with Hibitane® vaginal cream 8 ml every night for a week and then prophylactic treatment with 8 ml/week for another 11 weeks

or

- Reference treatment with Fluconazole® 150 mg (oral capsule) every 3 days for the first 3 doses, then prophylactic treatment with 150 mg/week for another 11 weeks

Please see section 7 for more details on randomization and study treatments.

Figure 1 Study design

| **Visit** | **1** | **2** | **3** | **4** | **5** |
| --- | --- | --- | --- | --- | --- |
|  |  | CHG | Chlorhexidine gluconate  vaginal application  8 ml/w, 11 w | |  |
|  |  | 8 ml/day,1 w  R |  |  | N=30 |
|  |  |  | Fluconazole  oral capsules  150 mg/w, 11 w | |  |
|  |  | FLZ  150 mg/day,1w |  |  | N=30 |
| **Week:** | **-1** | **0** | **1** | **12** | **24** |
|  | Screening | Inclusion/  Baseline  Randomization | Follow-up | Follow-up | Follow-up and end of treatment |

##

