### Biobank

All biopsy samples taken in this study will be registered in “Stockholm medical biobank” (register number 914, sample ID Bb142563) and handled according to the current biobank laws and regulations. The samples are coded/pseudonymized to protect the subject´s identification. All samples and the identification/code list are stored securely and separately to prevent unauthorized persons from having access to them.

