## Randomization

The randomization ratio between the treatment groups will be 1:1. A computer generated block randomization of 15 participants will be performed by the research midwife. Randomization to the study medications will be carried out via opening of opaque sealed envelopes in consecutive order. All women will be identified through a patient log with name and Swedish personal identification number and a study identification number, used on all CRFs (paper and electronic). The randomization will not be blinded to neither participants nor investigators due to the differences in study medications. The primary outcome variable is objective (negative vaginal culture for *Candida albicans*) with low risk of bias.

Subjects are included/randomized consecutively as they are found to be eligible for inclusion in the study. If a subject discontinues their study participation, their subject code will not be reused and the subject will not be allowed to re-enter the study again.

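### The protocol makes no provision for masking the biopsy reading of possible epithelial toxicity, a designated safety endpoint, to treatment arm or visit, although it masks the comparable lactobacilli photographs

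*Protocol*

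**What the plan says.** **Endpoint.** Item 7 of the list headed Secondary endpoint (variables) reads: "Proportion of women with possible toxic effect on the vaginal epithelium, defined as disruption and/or inflammation of the epithelial lining". Section 10.2.1 repeats the definition. No grading scale or threshold accompanies it.

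**Method.** Section 8.1.2, item 6, has biopsies taken at baseline and at the 3-month follow-up and examined by routine histopathology and immunohistochemistry, with PCR for antimicrobial peptides, cytokines and related markers. It adds: "Biopsies from participants allocated to FLZ will serve as controls". The reader is not named.

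**Role.** Section 8.2 lists this as one of the two secondary endpoints used for clinical safety; the other is adverse events. The synopsis and the background make absence of a cytotoxic effect one of the conditions for recommending the cream.

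**Blinding.** Section 7.6 (Blinding) is marked not applicable. Section 7.5 states: "The randomization will not be blinded to neither participants nor investigators due to the differences in study medications". Both 7.5 and Overall study design call the risk of bias low because the primary outcome, the culture, is objective.

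**Masking that is planned.** Section 8.1.2, item 4, on lactobacilli wet mounts: "These photos will be blinded and evaluated by the two investigators together".

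**Sample coding.** The Biobank section says: "The samples are coded/pseudonymized to protect" the subject's identity. It does not mention treatment arm or visit.

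**The concern.** A call of possible disruption or inflammation depends on judgement, and the word possible invites borderline calls. The two facts that define the comparison are the arm (cream or fluconazole control) and the visit (before or after). A reader who knows either may settle borderline slides differently, and the direction cannot be predicted: one reader may look harder for damage after the cream, another may give it the benefit of the doubt.

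The protocol's one argument for accepting an open design concerns the culture. It does not carry over to a histological judgement. At stake is the between-arm comparison on a named safety endpoint, and with it part of the support for saying that the cream does not harm the epithelium. The primary outcome is not affected.

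**Working it through.** **The plan's own figure.** The protocol gives no sample size, expected rate or margin for the biopsy endpoint. Its only calculation (section 10.4) is for the culture: 86% success in both arms, margin 30 points, power 90%. With one-sided alpha 5%, n per arm = (1.645 + 1.282)² × 2 × 0.86 × 0.14 / 0.30² = 22.9, so 23 per arm and 46 in total. The stated figure reproduces, but it has no bearing on masking.

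**The passages side by side.**

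| Question | Lactobacilli (8.1.2 item 4) | Epithelial toxicity (8.1.2 item 6, 8.2) |
|---|---|---|
| Read-out | Microscopy, normal or reduced | Microscopy, possible toxic effect or not |
| Rule for the call | Lactobacilli against epithelial cells per field | Disruption and/or inflammation, no scale |
| Compared across | Arms and visits | Arms and visits |
| Role | Secondary | Secondary, designated for safety |
| Masking stated | Yes | No |

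The endpoint with the looser rule and the safety role is the one without masking. No other part of the protocol fills the gap: 7.6 is not applicable, 7.5 and Overall study design leave participants and investigators unblinded, and the Biobank text is about identity.

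**Size of one call.** If all 30 women in an arm have an evaluable biopsy, one changed call moves that arm's proportion by 1/30 = 3.3 points. With the 23 per arm that the sample size calculation requires, it is 1/23 = 4.3 points. The protocol does not give the share of borderline slides, so the total bias cannot be computed.

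**Illustration of under-calling (all rates assumed).** Take 30 per arm, two-sided 5%, and a fluconazole reading rate of 5%. Power = Φ{[|p1 − p2| − 1.96·√(2p̄(1 − p̄)/n)] / √([p1(1 − p1) + p2(1 − p2)]/n)}, where p̄ is the mean of p1 and p2. If the reader calls only a share s of true findings in the cream arm, p1 becomes s × the true rate.

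| True cream-arm rate | s = 1 | s = 0.8 | s = 0.6 |
|---|---|---|---|
| 20% | 42% | 28% | 16% |
| 30% | 73% | 55% | 35% |
| 40% | 92% | 78% | 55% |

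For the 30% row at s = 0.8, p1 = 0.24, p2 = 0.05 and p̄ = 0.145. The numerator is 0.19 − 0.178 = 0.012 and the denominator 0.088, which gives about 55%. Moderate under-calling in one arm would cost much of the trial's ability to see a toxic effect. Over-calling would do the reverse and create a false signal. The protocol does not show that either would happen.

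**The case against.** The strongest reply is that silence is not an open reading. Section 7.6 sits among the treatment sections, next to code breaking, and 7.5 speaks of participants and investigators, not laboratory readers. The samples are coded, the code list is stored separately, and the laboratory work is done at core facilities, while section 11.1 lists only three study personnel. A reader there may not know the arm. **This stands in part.** A reader of the protocol might infer that the biopsies will be read open, but the text does not say so. Equally, it names no reader and withholds neither arm nor visit, so nothing prevents an arm-aware reading.

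Second, the toxicity conclusion also draws on PCR and immunological markers, which leave less to judgement. **True, and it limits the damage.** But the proportion to be reported is defined by disruption or inflammation of the epithelial lining, and immunohistochemistry is also read at the microscope.

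Third, one might infer that any reading error would be beyond repair. The documents do not support that: one biopsy is fixed in formalin and the samples are stored in a biobank, so a masked re-reading may be possible if tissue remains.

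Fourth, one might infer that five borderline calls would settle the comparison, because 5/30 against 0/30 gives a Newcombe 95% lower limit of +2.0 points. That assumes no fluconazole findings and 30 evaluable per arm. Fisher's exact test on the same table gives p = 0.052, before the false-discovery-rate control in section 10.3. With one fluconazole finding, 7 against 1 is needed for the Newcombe interval to exclude zero. The count is not a property of this plan.

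Fifth, methods not yet decided, or the unseen SAP, might cover the point. The deferral in the endpoint list belongs to item 8, the exploratory work, not to item 7. Masking of an assessor is trial conduct, and the protocol has a blinding section in which it could have been stated.

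**Conclusion.** The point holds as a gap in provision. The protocol does not secure masking of the biopsy reading to arm or visit for a subjective yes/no endpoint that it designates for safety, although it does so for a similar microscopy endpoint. Sample coding is described for privacy only, and the objectivity argument covers only the culture.

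The possible bias can go either way and its size is unknown. One call is worth 3.3 points with 30 evaluable women per arm, or 4.3 points with 23. The power figures above rest on assumed rates and show only that moderate differential reading would matter at this sample size. PCR and other markers protect the conclusion in part. The documents do not support saying that the reading is open, that an error could never be recovered, or that a fixed number of calls would decide the result. The point is worth correcting before any slide is read, and it leaves the primary outcome untouched.

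**What to change.** Add to section 8.1.2, item 6, and section 8.2, item 2:

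- Histology slides and immunohistochemistry sections from both arms and both visits are relabelled with random numbers and mixed.
- The planned reader reads them in random order without access to arm or visit.
- The code is linked to arm and visit only after the toxicity calls are locked.

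Someone other than the reader should do the relabelling and hold the key. Section 7.6 should then refer to the two masked readings, biopsies and lactobacilli photographs, instead of marking blinding as not applicable throughout.

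**Cost.** A small amount of relabelling of samples that are already coded. It needs no further biopsy or visit and no extra reader, since the lactobacilli photographs are already to be read masked by the investigators themselves. One limit remains: baseline biopsies come from women with symptomatic, culture-positive infection, so the tissue itself may hint at the visit. Masking removes the label, not that clue, but it still protects the comparison between arms.
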